### 3.2.6 Study Timeline

For all interventions with the exception of the START model, enrollment will occur for a four-six months period (Months 10-15 on Study Timeline). Enrollment will begin on Day 1 of the enrollment period and will stop either after the target number of patients are enrolled or at the end of the four-six months enrollment period (whichever comes sooner). Implementation will occur for a twelve-month period (Months 16-27 on Study Timeline). Outcome (retention) data will be measured at Month 27 of the study.

## 3.3 Objective 3: Methodological Toolkit

After analysis and synthesis of data collected during Objectives 1 and 2, the study team will develop a methodological toolkit that can be used to assess the feasibility, acceptability, needs, and preferences for differentiated models of care in other contexts and provide guidance for implementation of each model. Data will be collected using work process tracking and review with study staff members; cost tracking; and interviews with study staff and key decision makers. We will describe the processes required for assessing community ART needs, including identification of appropriate stakeholders for IDIs and FGDs, analysis of time taken to complete all data collection with a focus on understanding the key resources, and other inputs necessary to replicate these activities. Work process review will include quantification/counting of work activities and timing. Cost data will be tracked according to required accounting procedures. Qualitative data, including interview transcripts capturing information on the interactions between HIV patients and professional and lay health care workers that support various models of care, will be analyzed using grounded theory methods including the application of inductive and deductive codes. In addition, the toolkit will be informed by structured consultations (e.g. debriefing sessions) with qualitative research assistants and survey/DCE enumerators to identify key challenges encountered in the data collection process. The toolkit will be designed to be easily digestible and result in actionable plans to move from current standards to viable differentiated care models in a variety of circumstances and contexts. Based on input from reviewers, we will finalize the toolkit and provide it in both a downloadable digital and hard copy form with dissemination events with the MoH, MCDMCH and other appropriate national and sub-national stakeholders.

# 7.0 Appendices

## 7.1 Appendix 1: Selected Differentiated Care Model Outcome Studies

| **Study & Year (Please refer to References above for details)** | **Country** | **Study type** | **General strategy** | **Differentiated Model Element** |
| --- | --- | --- | --- | --- |
| Jaffar 2009 | Uganda | Cluster randomized trial | Down-referral to home (decentralization) and care by trained field officer (task shifting) every month compared to HIV clinic visit by MD every two months  Up-referral for positive symptom or adverse effect screen. | Service location  Health-worker cadre  Service frequency |
| Humphreys 2010 | Swaziland | Non-randomized trial | Down-referral to primary health center (decentralization) and care by nurse (task shifting) compared to hospital based care by MD  Up-referral when RN had questions about care | Service location  Health-worker cadre |
| Selke 2010 | Kenya | Cluster randomized trial | Down-referral to home (decentralization) and care by peer with PDA support (task shifting) every three months compared to HIV clinic visit with RN every month  Up-referral if PDA triggered alarm based on inputted symptoms, vital signs, pill count | Service location  Health-worker cadre  Service frequency |
| Babigumira 2011 | Uganda | Retrospective cohort | Down-referral to receive ART by pharmacy based nurse (task shifting) every month  Up-referral for “major clinical or social problems” or non-adherence | Health-worker cadre |
| Brennan 2011 | South Africa | Propensity matched retrospective cohort | Down-referral to primary health center (decentralization) and care by nurse (task shifting) every 2 months vs HIV clinic visit with MD every 6 months.  Up-referral for missed clinic visit or detectable viral load | Service location  Health-worker cadre  Service frequency |
| Fairall 2012 | South Africa | Cluster randomized trial | Down-referral to primary health center (decentralization) and care by nurse (task shifting) compared to hospital HIV clinic by MD  Up-referral based on criteria specified in national guidelines | Service location  Health-worker cadre |
| Kipp 2012 | Uganda | Prospective cohort | Down-referral to home (decentralization) and care by community volunteers (task shifting) every week.  Up-referral for positive symptom or adverse effect screen. | Service location  Health-worker cadre  Service frequency |
| Luque-Fernandez 2013 | South Africa | Retrospective cohort | Down-referral to community (decentralization) and care by peer or lay counsellor (task shifting) every 2 months | Service location  Health-worker cadre |

## 7.2 Appendix 2: Outcomes Framework

##
[figure not shown]

## 7.3 Appendix 3: Objective 1 Overview

| **Study Population** | **Measurements** | **Number of Sites/Sampling Approach** | **Sample Size** |
| --- | --- | --- | --- |
| Government and community leaders | In-depth interviews (qualitative) | - National: Individuals from MOH, MCDMCH, CMS, Central Laboratory - District Health Officers - Local community leaders - Implementing partners/civil society organizations | 20 interviews or until thematic saturation reached |
| Professional health care workers (doctor, nurse, pharmacist, clinic in-charge) | Focus Group Discussion (qualitative) | - Within each of three provinces (Lusaka, Southern, Eastern): 2 FGDs (1 Urban & 1 Rural) - 1 In-charges only FGD in Lusaka Urban District | 8 participants per FGD x 7 FGDs= 56 total participants |
| Lay/community health care workers | Focus Group Discussion (qualitative) | - Within each of three provinces (Lusaka, Southern, Eastern): 2 FGDs (1 Urban & 1 Rural) | 8 participants per FGD x 6 FGDs= 48 total participants |
| Family members of PLWHIV | Focus Group Discussion (qualitative) | - Within each of three provinces (Lusaka, Southern, Eastern): 2 FGDs (1 Urban & 1 Rural) |  |
| ART patients | Focus Group Discussion (qualitative) | - Within each of three provinces (Lusaka, Southern, Eastern): 4 FGDs (2 Urban & 2 Rural) | 8 participants per FGD x 12 FGDs= 96 total participants |
|  | General survey (quantitative) | - Within each of three provinces (Lusaka, Southern, Eastern): 2 urban & 2 rural clinics - Random sample of patients visiting a survey clinic will be approached for participation. | 800 |
|  | Medical record review (quantitative) | Same as for general survey | Same as for general survey |
|  | Discrete choice survey (quantitative) | - The first 500 patients consented to complete the general survey will be asked to complete the discrete choice survey. | 500 |
| Pre-ART patients | Focus Group Discussion (qualitative) | - Within Lusaka province only: 2 FGDs (1 Urban & 1 Rural) | 8 participants per FGD x 2 FGDs= 16 total participants |
|  | General survey (quantitative) | - Within each of three provinces (Lusaka, Southern, Eastern): sampling will occur at 2 urban and 2 rural clinics - Random Sample of patients visiting a survey clinic will be approached for participation. | 800 |
|  | Medical record review (quantitative) | Same as for general survey | Same as for general survey |

## 7. 4 Appendix 4: Overview of four models of differentiated care implemented in Objective 2

| **Model** | **Location** | **Number of sites** | **Number groups per site** | **Total sample size** | **Problem(s) addressing** | **Description of model** | **Selected related literature** |
| --- | --- | --- | --- | --- | --- | --- | --- |
| Model 1: Community adherence groups (CAGs) | Rural | 5 | 20 groups of 6 patients | 600 | Poor adherence and retention; long patient travel time and cost; rural clinic congestion and wait time | Monthly patient ART groups, facilitated by lay counselor, meet at location of group’s choice. Patients travel to clinic once every six months (rotating between group members) for labs and to pick up medications. | Decroo et al, 2011  Rasschaert et al, 2014 |
| Model 2: Urban adherence groups (UAGs) | Urban | 5 | 4 groups of 30 patients | 600 | Poor adherence and retention; long patient wait time and cost; urban clinic congestion | 2-3 monthly patient ART groups, meet during off-hours at clinics. Adherence discussion by lay ART counselor; ARVs distributed by pharmacy technician. Patients schedule clinic visit once every six months. | Luque –Fernandez, 2013 |
| Model 3: FAST-TRACK | Urban | 2 | N/A | 400 | Urban clinic space limitations/ congestion; wait time; poor retention | Container unit or dedicated room at clinics provide ART patients with rapid refills and health checks, facilitated by use of electronic health card. | McGuire et al, 2011  CIDRZ/MIT operational observation |
| Model 4: START | Urban & rural | 4 | N/A | 400 | Poor retention in newly eligible patients; clinic congestion and wait time | Patients testing positive will be given an option to move into a streamlined process wherein substantial counseling is delivered, as well as necessary baseline safety laboratory tests and ART is provided as soon as possible after being classified as eligible to initiate ART per guidelines. | Karim, 2009  Blanc, 2010  Amuron, 2009  Geng, 2011 |

## 7.5 Appendix 5: Routine schedule of activities within four models of differentiated care implemented in Objective 2

| Model | Frequency of Activity (interaction) | Symptom Screen | Interaction with clinician | Drug dispensation | Primary HCW Interaction |
| --- | --- | --- | --- | --- | --- |
| 1: Community Adherence Group | Monthly | Every visit | Every 6 months or acute event | Monthly | Lay health care worker |
| 2: Urban adherence Group | Every 2-3 months | Every visit | Every 6 months or acute event | Every 2-3 months | Lay health care worker |
| 3: Fast-Track | Every 3 months | Every visit | Every 6 months or acute event | Every 3 months | Pharmacy technician |
| 4: START | Intense initial ART facility interaction until ART initiation | Every visit | Every visit until ART initiation | At initiation | Clinical officer |

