*Discrete choice survey:* We will use Discrete Choice Surveys (DCSs) to assess patient preference for different, discrete characteristics of various models of community-based ART delivery. We will select key attributes (or aspects) of community-based ART models (i.e. frequency of facility visit, method of ART pick-up, type of health care worker, etc). Additionally, we will select the number of levels (or options) for each attribute (i.e. for frequency of facility visit: every 3 months or every 6 months). These will be used to create a list of all possible combinations. We will divide the subset of combinations chosen in blocks, so that each participant is only asked one possible block of the subset for a total of approximately 10 questions each.

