### 3.1.5 Sampling Approach/Sample Size Considerations

We have used convenience sampling to determine the number of interviews and focus groups to be conducted (see 1-6 below)

1. Government and community leaders: 20 interviews or until thematic saturation is reached.

2. Professional HCW: two focus group discussions will be conducted (one in an urban clinic and one in a rural clinic) in each province (EP, SP and LP).

3. Lay/Community HCW: two focus group discussions will be conducted (one in an urban clinic and one in a rural clinic) in each province (EP, SP and LP).

4. Patient family members: two focus group discussions will be conducted (one in an urban clinic and one in a rural clinic) in each province (EP, SP and LP).

5. ART patients: four focus group discussions will be conducted (two in an urban clinic and two in a rural clinic) in each province (EP, SP and LP).

6. Pre-Art patients: two focus group discussions will be conducted (one in an urban clinic and one in a rural clinic) in Lusaka province only.

We used the following sample size considerations to determine the number of surveys to be conducted:

General survey: 1,600 patients (of which 800 are ART and 800 are pre-ART).

To derive this sample size we considered a precision approach and calculated the number of ART participants necessary to estimate a binary indicator with 5% margin of error and 95% confidence interval. It is a common practice to assume a prevalence p=0.5 when several indicators are of interest, because p=0.5 is the most conservative choice. We also assume a design effect of 2 since our sampling is clustered at the facility level, and there is significant variability across facilities. Using the formula, we get: n=((1.96^2) * 0.5* 0.5 *2)/(0.05^2)=768, which we approximate at 800. The calculation is repeated for pre-ART patients.

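### Giving the discrete choice survey to the first 500 general-survey consenters lets fieldwork order decide how far each clinic and province is represented

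*Protocol*

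**What the plan says.** In Appendix 3 (Section 7.3), the ART-patient block has a general survey row and a discrete choice survey row.

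- **General survey sites:** "Within each of three provinces (Lusaka, Southern, Eastern): 2 urban & 2 rural clinics", with a sample size of 800.
- **General survey selection:** "Random sample of patients visiting a survey clinic will be approached for participation".
- **Discrete choice survey selection:** "The first 500 patients consented to complete the general survey will be asked to complete the discrete choice survey", with a sample size of 500.

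Section 3.1.5 confirms the parent sample ("General survey: 1,600 patients (of which 800 are ART and 800 are pre-ART") and bases its size on clustering: "We also assume a design effect of 2 since our sampling is clustered at the facility level, and there is significant variability across facilities". Section 3.1.3 gives the purpose of the choice survey, which is "to assess patient preference for different, discrete characteristics of various models of community-based ART delivery". The blocks described there divide the choice questions among participants; they do not allocate participants by site. None of Sections 3.1.3, 3.1.5 and 7.3 sets a cap, quota or random subsample by clinic, province or urban/rural setting for the 500, gives the order in which clinics start, or derives the figure of 500.

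**The concern.** The general survey is laid out over three provinces and both settings, with random approach of patients inside each clinic. The choice survey takes a subset of those patients by date of consent. Random approach within a clinic does not protect a subset that is cut off by calendar time across clinics. Once 500 have consented, every patient enrolled later is left out, whatever the clinic. Clinics that open early or recruit quickly therefore carry more weight than they have in the parent sample.

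This matters because the protocol itself expects facilities to differ. If preferences differ between provinces or clinics, a pooled preference estimate depends on the mix of sites, and under this rule logistics set the mix. Weighting afterwards can correct uneven shares, but it cannot supply a province that has no respondents.

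**Working it through.** **Inputs.** 800 ART patients and a design effect of 2 (Section 3.1.5); 3 provinces with 4 clinics each, so 12 clinics, and 500 choice-survey patients (Section 7.3). *Assumption:* equal shares per clinic and province, because the protocol gives none.

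**The plan's own figure.** Section 3.1.5 aims to "estimate a binary indicator with 5% margin of error and 95% confidence interval" and computes "n=((1.96^2) * 0.5* 0.5 *2)/(0.05^2)=768, which we approximate at 800". Check: 1.96² × 0.5 × 0.5 × 2 / 0.05² = 768.3, which agrees. There is no stated calculation for the 500 to reproduce.

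**How quickly 500 fills.**
- Per clinic: 800/12 = 66.7. Per province: 800/3 = 266.7.
- Two provinces: 2 × 266.7 = 533, which exceeds 500.
- Clinics needed to fill 500: 500/66.7 = 7.5 of 12.

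**Strictly sequential provinces.** 267 from the first, 500 − 267 = 233 from the second, 0 from the third.

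**Two provinces together, the third starting late.** Let each province recruit r = 266.7 per unit of its own fieldwork time, and let the third start after a delay d in the same unit. The survey fills at the time t that solves 2rt + r(t − d) = 500, so the third province contributes r(t − d) = 266.7 × (1.875 − 2d)/3, where 1.875 = 500/266.7.

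| Delay d | Third province |
| --- | --- |
| 0 | 167 |
| 0.25 | 122 |
| 0.5 | 78 |
| 0.75 | 33 |
| 0.9375 or more | 0 |

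**All start together at unequal speeds.** Each province contributes 500 × its speed / sum of speeds (none reaches its ceiling of 267 here).
- 1:1:1 gives 167/167/167.
- 2:2:1 gives 200/200/100.
- 3:2:1 gives 250/167/83.
- 4:4:1 gives 222/222/56.

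**What this does to a pooled estimate.** Take a simple proportion preferring some option, and suppose the third province differs by D from the other two, which agree with each other. Against equal thirds, the pooled proportion shifts by D × (1/3 − s), where s is the third province's share of the 500.
- s = 0: shift of 0.33 D.
- s = 56/500 = 0.11: shift of 0.22 D.
- s = 100/500 = 0.20: shift of 0.13 D.

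D is not given in the protocol. If D is zero there is no bias.

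**Urban against rural.** In the sequential case the first province is complete, with about 133 urban and 133 rural. The second gives 233 of 267. Even if the missing 33 all come from one setting, the total is about 267 against 233.

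**The case against.** The strongest reply is that the harm depends on fieldwork facts the protocol does not state. Clinic shares and start order are not given, and a simultaneous start at equal speed gives 167 per province with nothing lost. That stands, and it makes the point conditional.

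Three stronger readings are tempting, and the documents do not support them.
- A reader might infer that quick recruitment elsewhere could by itself drop a province. In the ranges tried it does not: even at 4:4:1 the slowest province supplies 56. An empty province needs sequential or strongly staggered fieldwork, with a delay of about 94% of a province's fieldwork time when the other two run together.
- A reader might infer that the urban/rural balance is lost. Province-by-province fieldwork does not do this, because every province has two clinics of each kind. Imbalance would need a visiting order by setting, which is not stated.
- A reader might infer that a planned urban/rural or provincial comparison is undermined. Section 3.1.4 plans main effects and two-way interactions in a nested logit and names no such contrast for the choice survey. What is exposed is the pooled estimate.

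It is also fair to say that Objective 1 has other sources. The general survey and the ART-patient focus groups cover all three provinces and both settings, and Section 3.1.4 cross-references qualitative and preference data. This softens the consequence, but neither source replaces the choice experiment's own estimates. The convenience-sampling sentence in Section 3.1.5 introduces the interviews and focus groups, so it does not justify the rule for the 500.

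**Conclusion.** The point holds as a conditional risk to representativeness. The protocol fixes a calendar-order rule with no safeguard by site, and under equal shares 7.5 of 12 clinics are enough to fill it. The third province's contribution runs from 167 (simultaneous start, equal speed), through 100 (speeds 2:2:1) or 78 (a half-length delay), to 0 (strictly sequential fieldwork). These figures rest on equal shares per clinic and on start orders and speeds that are assumed. Bias in the pooled preferences follows only if sites differ, which Section 3.1.5 leads one to expect. It would be wrong to say that the rule will bias the result or that a province will be missed. The matter is confined to the preference component of Objective 1; the Objective 2 retention and ART-initiation outcomes and their power are untouched. It is a modest flaw with an inexpensive remedy.

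**What to change.** In Appendix 3, replace the calendar-order rule with random selection at every survey clinic: offer the choice survey to a random five in eight (500/800 = 0.625) of consenting ART general-survey participants. With equal shares this gives 500/12 = about 42 per clinic and 500/3 = about 167 per province. Section 3.1.3 already has enumerators entering the general survey on tablets, so a random flag there is one practical way to do it, if the choice survey is run in the same session. An equivalent quota per clinic would also serve.

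The planned sample size does not change. There are two costs. Staff must be ready to run the choice survey at all 12 clinics until fieldwork ends. The total also follows the general survey, so if that stops at 768, five in eight gives 480. If the survey has already been run under the present rule, report the choice-survey counts by clinic, province and urban/rural site beside the estimates.

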## 7.6 Appendix 6: Power calculations for Objective 2: CAG and UAG

| Alpha | Pi0 | Pi1 | K | J | N | Power |
| --- | --- | --- | --- | --- | --- | --- |
| **Modify Pi0 and Pi1** |  |  |  |  |  |  |
| 0.05 | **0.8** | **0.6** | 0.1 | 30 | 5 | 0.62 |
| 0.05 | **0.8** | **0.4** | 0.1 | 30 | 5 | 0.997 |
| 0.05 | **0.7** | **0.5** | 0.1 | 30 | 5 | 0.63 |
| 0.05 | **0.6** | **0.4** | 0.1 | 30 | 5 | 0.66 |
| 0.05 | **0.6** | **0.3** | 0.1 | 30 | 5 | 0.96 |
| 0.05 | **0.4** | **0.2** | 0.1 | 30 | 5 | 0.7989 |
|  |  |  |  |  |  |  |
| **Modify k** |  |  |  |  |  |  |
| 0.05 | 0.6 | 0.3 | **0.1** | 30 | 5 | 0.96 |
| 0.05 | 0.6 | 0.3 | **0.2** | 30 | 5 | 0.82 |
| 0.05 | 0.6 | 0.3 | **0.3** | 30 | 5 | 0.597 |
|  |  |  |  |  |  |  |
| **Modify j** |  |  |  |  |  |  |
| 0.05 | 0.6 | 0.3 | 0.1 | **10** | 5 | 0.64 |
| 0.05 | 0.6 | 0.3 | 0.1 | **15** | 5 | 0.7988 |
| 0.05 | 0.6 | 0.3 | 0.1 | **30** | 5 | 0.96 |
| 0.05 | 0.6 | 0.3 | 0.1 | **45** | 5 | 0.991 |
| 0.05 | 0.6 | 0.3 | 0.1 | **90** | 5 | 0.999 |
| 0.05 | 0.6 | 0.3 | 0.1 | **120** | 5 | 0.999 |
|  |  |  |  |  |  |  |
| **Modify n** |  |  |  |  |  |  |
| 0.05 | 0.6 | 0.3 | 0.1 | 30 | **5** | 0.96 |
| 0.05 | 0.6 | 0.3 | 0.1 | 30 | **6** | 0.99 |
| 0.05 | 0.6 | 0.3 | 0.1 | 30 | **7** | 0.997 |

alpha= significance level

Pi0= baseline proportion

Pi1=post-intervention proportion

k=co-efficient of variation

j= sample size per cluster

n= number of matched cluster
